### Standardisation of postoperative management

As this is a pragmatic RCT, postoperative care and the criteria for drain removal will be in accordance with local practice. However, we have identified two elements of patient care, which require standardisation to minimise the potential for bias, namely pain-control and the criteria by which a participant’s medical fitness-for-discharge is assessed.

Standardising the use of analgesia across participating centres is impractical and does not reflect the intended pragmatic nature of the trial, it, would also produce data unrepresentative of real clinical practice. Therefore, each participating centre will prescribe analgesia in accordance with their local protocols. All patients recruited to the RCT at that centre will be given the same analgesia regardless of their treatment allocation (ie, VATS lobectomy or open lobectomy). Local protocols for the provision of analgesia will be defined by the local Principal Investigator (in collaboration with the local research team) prior to the start of recruitment to the RCT. Analgesia administered throughout the participant’s in-hospital stay will be recorded on the trial case report forms (CRFs) and compliance with the predefined and centre-specific analgesia protocols will be monitored.

In order to objectively compare the time from surgery to hospital discharge between VATS lobectomy and open lobectomy, the following discharge suitability criteria have been developed. Study participants will be evaluated against these criteria to ensure that they are medically fit-for-discharge:

Participant has achieved satisfactory mobility.Pain under control with analgesia.Satisfactory serum haemoglobin and electrolytes (ie, does not require intervention).Satisfactory chest X-ray (which will be performed as part of routine clinical care).No complications that require further/additional treatment.

Participants who are considered medically fit-for-discharge may not necessarily be discharged immediately; in some instances, social and other factors may necessitate extended hospitalisation. The time at which participants are considered medically fit-for-discharge and when they are physically discharged from hospital will both be recorded on the trial CRFs.

### Sample size calculation

We hypothesise that self-reported physical function (scale 0–100, with higher scores indicating better function) 5 weeks after randomisation for participants undergoing a VATS lobectomy will be superior to the physical function for participants having an open lobectomy, as measured using the EORTC QLQ-C30. The sample size has been chosen to test this hypothesis.

Although the primary endpoint is at 5 weeks post-randomisation self-reported physical function will also be assessed at other time points (baseline, 2 weeks, 3 months, 6 months and 1 year). In estimating the sample size these additional measurements have been taken into account. The power calculation requires the estimation of four parameters (ie, the effect size that would be considered clinically important, the number of pre-surgery and post-surgery measures, and the correlations between pre-surgery and post-surgery scores and between repeated post-surgery scores). The effect size was chosen based on the published literature,^19^ which suggests that an effect size of 0.2 to 0.6 SD equates to a clinically important difference in physical function score of between 5 and 14 points or approximately a one category change in performance status. In the absence of data from which to estimate the correlations between repeated measures, we assumed conservative estimates (0.3 between pre and post measures, 0.6 between repeated post measures).

The study size has been set at 398; allowing for a 20% dropout at 1 year, the target sample size is 498 participants. This will provide 90% power to test the hypothesis, assuming an effect size of 0.25 SD in physical function would be clinically important. The calculation based on five postsurgery measures assumes the treatment difference is similar at the five time points.

However, it is anticipated that the difference in physical function may change over time. The calculation based on a single measure shows that the study will have >80% power to detect a difference of 0.25 SD and >90% power to detect a difference of 0.3 SD at the primary endpoint where dropout is expected to be less than 5%.

A study in 498 participants will also have 80% power to detect a 1 day difference in length of hospital stay (ie, median 3 days vs 4 days, HR 1.3); assuming 2% of patients do not survive to discharge.

### Research procedures

Generic and disease-specific HRQoL measures will assess the profiles of VATS and open lobectomy in the early and mid-postoperative phases. The extensively validated EQ-5D-5L will assess generic aspects of HRQoL and will be used in the economic evaluation.^20 21^ The EORTC QLQ-C30 is one of the most widely used instruments for assessing HRQoL in patients with cancer and the QLQ-LC13 is the lung cancer module with 13 items that assesses lung cancer–specific symptoms.

Study participants will be asked to complete HRQoL questionnaires at baseline and postoperatively at 2 weeks, 5 weeks, 3 months, 6 months and 1 year post-randomisation. Baseline questionnaires will be administered by the research team at site, whereas the questionnaires completed post-operatively will be administered by the coordinating centre. Participants can choose to receive post-operative questionnaires by post or complete via a secure website.

### Patient and public involvement

The Royal Brompton Hospital Cancer Consortia patient and public involvement (PPI) group were involved from inception and advised on trial design, identification of the choice and timing of the primary outcome, and secondary outcomes that were considered to be important. They were consulted between August 2012 and September 2013. The aim of PPI involvement in VIOLET was to advise on patient-orientated outcomes that matter. The group consists of four patients who have undergone surgery for cancer and one carer. [name], who is a patient, and a general practitioner by profession, has agreed to sit on the trial steering committee (TSC).

The PPI group will also be involved in reviewing the content and format of PILs and dissemination of the results of the study.

### Integrated QuinteT Recruitment Intervention

The VIOLET study will employ an integrated QuinteT Recruitment Intervention (QRI) to optimise and sustain recruitment throughout the recruitment period because recruitment is anticipated to be difficult. Although recruitment to RCTs is recognised as a research priority,^22^ there is a dearth of robust evidence about effective strategies to improve recruitment in RCTs.^23^ Surgical RCTs face specific recruitment challenges due to the complex nature of surgical procedures, the dependence on many healthcare professionals across disciplines and surgeon-related factors such as variations in individual practice/expertise.^24^ In addition, surgical RCTs, such as VIOLET, that compare minimally invasive and open operations have historically been difficult to conduct and recruit to.^25 26^

The QRI, employing primarily qualitative research methods can be used to understand recruitment in specific RCTs^27–29^ as well as across RCTs.^30–32^ It has been shown to optimise recruitment and informed consent, thereby contributing to successful recruitment and trial completion.^33–35^ In VIOLET, in order to understand the recruitment process at each centre in real time, investigate the sources of recruitment difficulties and address the challenges, some of the key methods employed^36^ will be as follows:

*Patient pathway through eligibility and recruitment:* A comprehensive process of logging potential trial patients through screening and eligibility phases will be undertaken to provide basic data about the levels of eligibility and recruitment, and identify points at which patients opt in or out of the RCT.

*In-depth interviews:* In-depth, semi-structured interviews will be conducted and audio-recorded with a purposive sample of staff members involved with aspects of trial design/management and recruitment across centres in phase 1 (and phase 2 where necessary). Patients eligible for recruitment to the RCT may also be interviewed. Across the different groups, interviews will explore participants’ perspectives of the trial, the two procedures and acceptability of randomisation between procedures. In addition, recruitment staff (primarily surgeons) interviews will explore their experiences of undertaking both procedures (where appropriate), perceptions of equipoise for themselves and their colleagues, and views on likely outcome of the trial. Interview topic guides will be used to ensure similar topic areas are covered across interviews, while still providing the scope for participants to raise issues of pertinence to them.

*Audio recording of recruitment appointments*: Face-to-face and telephone consultations of healthcare staff (thoracic surgeons, nurses etc) with potentially eligible patients will be routinely audio recorded across centres to understand the recruitment process at each centre and to identify and investigate the challenges to recruitment. The QRI researcher will listen to and qualitatively analyse the appointments, documenting instances such as unclear, insufficient or imbalanced information provision and unintentional transferring of clinician treatment preferences to patients.

An account of the anonymised findings from all the data will be fed back to the RCT chief investigator (CI), with a plan of action to optimise recruitment developed collaboratively with key stakeholders. The data will be used by the QRI team to provide supportive and confidential individual and group feedback to recruiters to help them to communicate equipoise, balance treatment options and explain to patients the benefits and purposes of trial participation, while optimising informed consent. Feedback sessions will include comparisons between what clinicians think they say to patients (interview data) and what they actually say to patients (consultation data). Rates of recruitment of eligible patients will be closely monitored against the feedback meetings, and it is expected that an improvement will be demonstrated in recruitment over time with experience and training for recruiters. (As we have demonstrated is possible in other similar trials.^27–29 33–35^)

### Economic evaluation

The economic evaluation will compare the costs and effects of VATS lobectomy versus open lobectomy, and will follow established guidelines as set out by the National Institute for Health and Care Excellence.^37^ The within-trial cost-effectiveness analysis will be undertaken from an NHS and personal social services perspective, with a 1 year time horizon from the day of surgery. The primary outcome measure for the economic evaluation will be quality-adjusted life-years (QALYs), estimated using the EuroQol EQ-5D-5L, administered at baseline (pre-randomisation) and five time points post-randomisation (see table 1). Resource use data collection will be integrated into the trial CRFs for the index admission for items such as duration of surgery, number of staples used and length of stay; and captured from participants regularly during the 1-year follow-up (see table 1) for events such as hospital readmissions, outpatient attendances and general practitioner (GP) or nurse visits in the community.

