### Aims and objectives

The VIOLET study will test the hypothesis that VATS lobectomy is superior to open lobectomy with respect to self-reported physical function 5 weeks after randomisation (approximately 1 month after surgery).

Specific objectives are to estimate:

The difference between groups in the average self-reported physical function at 5 weeks.The difference between groups with respect to a range of secondary outcomes including assessment of efficacy (hospital stay, pain, proportion and time to uptake of chemotherapy), measures of safety (adverse health events), oncological outcomes (proportion of patients upstaged to pN2 disease and disease-free survival) and overall survival.The cost-effectiveness of VATS lobectomy compared with open lobectomy.

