**Figure 2 F2:**
[figure not shown]
The trial schema showing the recruitment pathway for phase 2 of the VIOLET study. VATS, video-assisted thoracoscopic surgery; VIOLET, VIdeo assisted thoracoscopic lobectomy versus conventional Open LobEcTomy for lung cancer.

*Phase 1:* The first phase with an integrated qualitative component is necessary to establish the processes for recruitment and consent. This phase is also essential to develop a study manual and a measure of surgical expertise to proceed to phase 2. Phase 1 will be conducted in five centres; Royal Brompton Hospital in London, The University Hospitals Bristol in Bristol, Liverpool Heart and Chest Hospital in Liverpool, The James Cook University Hospital in Middlesbrough and Harefield Hospital in Harefield. These centres are well spread geographically and represent a mix of university and NHS trusts that are representative of NHS practice. Progression from pilot to the full trial will be dependent on preagreed progression criteria (assessed after 18 months of recruitment):

Specifically:

At least 60% of patients undergoing lobectomy are considered eligible for the trial (if necessary, by revising the eligibility criteria).At least 50% consent to randomisation after 6 months of recruitment.Less than 5% fail to receive their allocated treatment.Less than 5% lost to follow-up, excluding deaths.

*Phase 2:* This phase will extend the study to up to a further five centres. All centres will use the optimum methods of recruitment established in phase 1 and will follow-up all participants to 1 year.

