### Randomisation

Participants will be randomised in a 1:1 ratio to either VATS lobectomy or open lobectomy. Randomisation will take place through a secure internet-based randomisation system, access to which will be restricted to authorised study personnel. Cohort minimisation (with a random element incorporated) will be used to ensure balance across groups with respect to the surgeon and the allocation will be stratified by centre.

Due to the pragmatic nature of this trial there will inevitably be some variability between surgeons, the surgical teams and the perioperative processes. Such heterogeneity is important as this accurately reflects real clinical practice.

Randomisation will be performed 1 week prior to the planned operation date, once eligibility has been confirmed and written consent taken by a research nurse. This will allow sufficient time for operating theatre schedules to be arranged. If there is a change in surgeon after randomisation, the analysis will account for the surgeon responsible for performing the operation and not the surgeon originally allocated to the patient.

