### Primary and secondary outcomes

The primary outcome is self-reported physical function measured using the European Organization for Research and Treatment of Cancer Quality of Life Questionnaire-C30 (EORTC QLQ-C30) at 5 weeks post-randomisation. Physical function has been chosen because it is a patient-centred outcome that will reflect the anticipated earlier recovery with VATS lobectomy and has been used in other minimal access surgery trials. The primary endpoint has been chosen to be 5 weeks (1 month post-surgery) to capture the early benefits of minimal access surgery on recovery. The EORTC QLQ-C30 has been validated for use in European cohorts. In addition to assessing physical function the questionnaire also assesses psychological and social well-being. Secondary outcomes have been selected to assess the efficacy of the two approaches.

Secondary outcomes are (1) time from surgery to hospital discharge; (2) adverse health events; (3) proportion and time to uptake of adjuvant treatment; (4) proportion of patients upstaged to pN2 disease after the procedure; (5) overall and disease-free survival to 1 year; (6) proportion of patients who undergo complete resection during the procedure; (7) proportion of patients who experience prolonged incision pain defined as the need for analgesia >6 weeks after surgery; (8) generic and disease-specific health-related quality of life (HRQoL) assessed using the EORTC QLQ-C30, QLQ-LC13 and EQ-5D-5L questionnaires completed at 2 weeks, 5 weeks, 3 months, 6 months and 1 year post-randomisation); (9) resource use measured for the duration of post-operative hospital stay until discharge and at 5 weeks, 3 months, 6 months and 1 year post-randomisation.

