### Data collection

The schedule of data collection for the study is shown in table 1. Data will be collected on paper and then entered onto a bespoke database. Access to the database will be via a secure password-protected web-interface (NHS clinical portal). Study data transferred electronically between the University of Bristol and the NHS will only be transferred via a secure NHS.net network in an encrypted form.

**Table 1 T1:** Data collection for trial participants who agree to randomisation to VATS lobectomy or open lobectomy

	Pre-randomisation	Post-randomisation								
	Baseline	Day of surgery	Postop	2 days postop	Discharge	2 weeks*	5 weeks*	3 months*	6 months*	1 year*
Eligibility	*X*									
Imaging review (CT/Positron Emmission Tomography (PET)--CT†)	*X*									
Participant characteristics	*X*									
Audio recorded consultation	*X*									
Lobectomy via VATS lobectomy or open lobectomy		*X*								
Intraoperative details		*X*								
Histopathology staging		*X*								
Tumour sample for research		*X*								
Patient questionnaires										
QLQ-C30	*X*					*X*	*X*	*X*	*X*	*X*
QLQ-LC13	*X*					*X*	*X*	*X*	*X*	*X*
EQ5D	*X*					*X*	*X*	*X*	*X*	*X*
Bang Blinding Index				*X*	*X*					
Pain score	*X*		*X*	*X*						
Adverse events		*X*					*X*	*X*	*X*	*X*
Resource use	*X*	*X*					*X*	*X*	*X*	*X*
CT scan of chest and abdomen										*X*

*Follow-up time-points will be calculated from the date of randomisation.

†Review of images available from staging scans performed in accordance with standard practice at participating centres.

QLQ, Quality of Life Questionnaire; VATS, video-assisted thoracoscopic surgery.

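### The economic horizon is counted from surgery but its data are scheduled from randomisation, so the last planned week has no scheduled data and a participant who is never operated on has no start date

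*Protocol article*

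**What the plan says.** All references are to the protocol article.

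- **Economic evaluation:** the cost-effectiveness analysis is planned "with a 1 year time horizon from the day of surgery". The same paragraph has the EQ-5D-5L, from which QALYs are derived, "administered at baseline (pre-randomisation) and five time points post-randomisation".
- **Data collection, footnote to Table 1:** "Follow-up time-points will be calculated from the date of randomisation".
- **Primary and secondary outcomes, item 9:** "resource use measured for the duration of post-operative hospital stay until discharge and at 5 weeks, 3 months, 6 months and 1 year post-randomisation".
- **Randomisation:** "Randomisation will be performed 1 week prior to the planned operation date".
- **Trial design, Phase 2:** centres "will follow-up all participants to 1 year". No visit is scheduled at one year after surgery.
- **Statistical analysis plan:** the data are to be analysed by intention to treat, and missing resource-use and EQ-5D-5L data are to be multiply imputed.

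The article keeps the two clocks apart elsewhere. Aims and objectives places the primary endpoint "5 weeks after randomisation (approximately 1 month after surgery". The day of surgery therefore cannot be read as loose wording for the date of randomisation.

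**The concern.** The horizon and the data that fill it have different origins, with three consequences.

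1. The horizon ends after the last scheduled questionnaire, so its final stretch has to be extrapolated. Multiple imputation replaces scheduled values that are missing. Beyond the last scheduled point there are no values by design for it to draw on.
2. Surgery happens after allocation. Starting the clock there removes the interval between randomisation and operation from a randomised comparison.
3. A participant who dies, withdraws or becomes inoperable before theatre has no day of surgery, hence no defined one-year window, although intention to treat requires that participant to be counted.

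Cost-effectiveness is one of the trial's stated objectives. If the wording stays as it is, the alignment of the two clocks may be chosen once data are in hand.

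**Working it through.** **Inputs from the article.** Planned gap from randomisation to surgery: 7 days. Horizon: 1 year (365 days) from surgery. Last scheduled EQ-5D-5L and resource-use collection: 1 year (365 days) from randomisation. Target sample: 498.

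**Assumed inputs, not in the article.** Between-arm utility difference late in the year: 0.02 to 0.10. Longer gaps if surgery is postponed: 14, 28 and 42 days.

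**Step 1. Reproduce the article's own conversion between the clocks.** Days from surgery = days from randomisation − gap. For the primary endpoint, 35 − 7 = 28 days, about one month. This agrees with Aims and objectives, so a 7-day offset is what the authors intend.

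**Step 2. Place the horizon on the randomisation clock.**
- Start: day 7. End: 7 + 365 = day 372.
- Last scheduled data: day 365.
- Tail without scheduled data: 372 − 365 = 7 days, and 7/365 = 1.9% of the horizon.

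The tail always equals the gap. At assumed gaps of 14, 28 and 42 days it would be 14/365 = 3.8%, 28/365 = 7.7% and 42/365 = 11.5%.

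**Step 3. Comparative information in the tail when the gap is equal in both arms.** Incremental QALY in the tail = utility difference × 7/365.

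| Assumed late utility difference | QALY in the missing week |
|---|---|
| 0.02 | 0.0004 |
| 0.05 | 0.0010 |
| 0.10 | 0.0019 |

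**Step 4. Participants without a time zero.** The article does not give their number. The pilot progression criterion allows fewer than 5% not to receive their allocated treatment. If that held in the full trial, the ceiling would be 0.05 × 498 = 24.9, so fewer than 25. The criterion also counts crossovers, so this is an upper limit and not an estimate. A participant who has a frozen-section biopsy and no lobectomy still has a day of surgery and is not in this group.

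**Step 5. Repeat with randomisation as origin.** The horizon runs from day 0 to day 365, the tail is 365 − 365 = 0 days, and every randomised participant has a start date.

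**The case against.** The strongest case on the other side is that this is a wording slip with little effect. Much of that case stands.

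- **Bias between arms.** A reader might infer that the mismatch biases the incremental QALY. At an assumed utility of 0.8, a 3-day difference between arms in time to surgery gives 0.8 × 3/365 = 0.007 QALY, and 5 days gives 0.8 × 5/365 = 0.011. The documents do not support this reading. It needs an arm difference that nothing in the article indicates: randomisation is timed against a date already planned, allocation is stratified by centre and minimised by surgeon, and all surgeons perform both operations. It also needs the tail to be scored as zero utility, which the article nowhere says. If the tail were filled from the one-year questionnaire with an assumed utility error of 0.05, the same differences would give 0.05 × 3/365 = 0.0004 and 0.05 × 5/365 = 0.0007.
- **Exclusion of unoperated participants.** A reader might infer that they will be dropped. The article does not say so, and the full protocol or analysis plan may assign them a start date. What stands is narrower: the origin as stated is undefined for them.
- **Baseline utility.** It is measured before randomisation, so it precedes time zero under either origin. It is no argument against the surgical origin.
- **Size of the gap.** One week is the planned gap, not a minimum. Questionnaires returned late, or obtained later by the research nurse, may cover part of the tail, but by chance and not by design.
- **The pre-operative week.** Neither operation has yet taken place and participants do not know their allocation, so costs and utility have little reason to differ between arms. The loss from omitting that week is probably small.

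The article's brevity does not answer the point itself. It fixes the horizon and the schedule explicitly, and the two do not match.

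**Conclusion.** The point holds as an internal contradiction of modest consequence. The stated horizon cannot be fully observed on the trial's own schedule: 7 of its 365 days (1.9%) lack scheduled utility and follow-up resource-use data at the planned gap, and more if surgery is postponed. It also places the origin of a randomised comparison after allocation, and leaves any randomised but unoperated participant without a start date, which does not fit intention to treat.

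The expected effect on the incremental QALY is about 0.0004 to 0.002. That rests on a similar time to surgery in both arms and on an assumed late utility difference of 0.02 to 0.10. No effect on incremental cost can be calculated from the article. The primary outcome is not affected. The correction is worth making because it is nearly free and settles the alignment in advance.

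**What to change.** In Economic evaluation, define the horizon as one year from randomisation, for both costs and QALYs and for every randomised participant whether or not operated on. This matches the Table 1 schedule and needs no extra visit.

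One check is needed. Costs between randomisation and surgery would now count. Item 9 of the outcomes describes the post-operative stay and the later follow-up points, and Table 1 marks resource use at baseline and on the day of surgery, but the article does not say which period each form covers. The sponsor should confirm that the forms capture the short pre-operative interval. If they do not, a small addition to a form or a stated costing assumption would be required.

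A horizon counted from surgery may be kept as a sensitivity analysis in operated participants, provided the rule for extrapolating beyond the last questionnaire is stated in advance.
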